#### Primary endpoint analysis

##### Randomisation 1

For R1, the number and proportion of participants, categorised as unfit or frail at baseline, experiencing an early treatment cessation event will be summarised by randomisation allocation and exact 95% CIs will be calculated.

A logistic regression model will regress early treatment cessation on randomisation allocation (reactive/adaptive dosing) adjusting for the stratification factors of the trial. A statistically significant induction treatment effect will be suggested if the p value for the resulting OR is <0.047. Parameter estimates, ORs and corresponding 95% CIs, df, test statistics and p values will be presented for each variable in the model. Residuals and predicted values produced from the models will be examined to assess the assumptions of the statistical models.

##### Randomisation 2

For R2, PFS between the two maintenance therapies (R+placebo/R+I) will be compared using a Cox regression model adjusting for the stratification factors of the trial. A statistically significant maintenance treatment effect will be suggested if the p value for the HR corresponding to randomisation allocation is <0.047. Parameter estimates, HRs and corresponding 95% CIs, df, test statistics and p values will be presented for each variable in the model.

The proportional hazards assumptions will be assessed by plotting the hazards over time (ie, the log cumulative hazard plot) for each treatment arm and using appropriate statistical tests. If evidence is found to support the violation of the proportional hazards assumption, then alternative appropriate analysis methods will be investigated.

No imputation strategy is planned for the primary endpoints.

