#### Treatment delivery

The International Myeloma Working Group (IMWG) proposed a scoring system for patient with myeloma frailty that predicts survival, adverse events (AEs) and treatment tolerability,^14^ which can help to account for the considerable heterogeneity in outcome for TNE patients. This score combines age and the outcomes of three patient assessment tools; the Katz Activity of Daily Living,^15^ Lawton’s Instrumental Activity of Daily Living^16^ and the Charlson Comorbidity Index^17 18^ to categorise patients into three groups: fit, unfit and frail. The IMWG frailty score was subsequently shown to be predictive of both PFS and toxicity. An increase in frailty score was associated with an increased risk of death, progression, non-haematological AEs and treatment discontinuation that was independent of classical definitions of risk, including ISS stage and cytogenetic risk, and also independent of treatment regimen. As such, it was suggested to be useful in determining the feasibility of treatment regimens and appropriate dose reductions, but this remains to be prospectively validated.

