#### Trial follow-up

Participants who discontinue treatment during induction and before the point of R2 will be followed up to the point of assessment for eligibility for R2, unless they withdraw consent for this. Thereafter, participants will continue to be followed-up for data pertaining to safety, progression (including second progression), and survival. Frailty scores will be completed for all participants at 2, 4, 6 and 12 months post R1, irrespective of whether they have discontinued treatment. Similarly, QoL and healthcare resources use questionnaires (if the participant has consented to these) will continue to be completed at 2, 6 and 12 months post R1.

If treatment has been stopped without progression following R2, for example, due to toxicity, then participants will be followed up 2 monthly until disease progression. Follow-up will include local investigations, central investigations, frailty index at 6 and 12 months post R2 and QoL and healthcare resource use at 6 and 12 months post R2 (if consented).

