### Randomisations

Following trial registration, patients will be assessed for R1 eligibility. Eligible participants will be randomised on a 1:1 basis into R1, using the stratification factors; centre, IMWG frailty category, beta-2 microglobulin concentration (<3.5, 3.5 to <5.5, ≥5.5 mg/L), Haemaglobulin concentration (<100, ≥100 g/L, serum crestinine concentration (<175, ≥175 µmol/L), corrected serum calcium concentration (<2.75, ≥2.75 mmol/L) and platelets (<150, ≥150×10^9^/L).

Following R1, and as soon as the end of induction response is known, R2 eligible participants will be randomised on a 1:1 basis into R2, using the stratification factors; centre, allocated induction arm (reactive, adaptive); final response to induction treatment (<VGPR, ≥ VGPR).

For both R1 and R2, a computer generated minimization programme that incorporates a random element will be used to ensure treatment groups are well balanced for the specified stratification factors.

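### The R2 Cox model, as naturally read, omits IMWG frailty category; the planned test and its 80% power stand, but a little extra power from data already collected is forgone

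*Protocol article*

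**What the plan says.** **Model.** Under Primary endpoint analysis, Randomisation 2: "PFS between the two maintenance therapies (R+placebo/R+I) will be compared using a Cox regression model adjusting for the stratification factors of the trial". The R1 logistic model is described with the same phrase about the trial's stratification factors. Under Secondary endpoint analysis, OS follows the PFS method.

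**Factors.** Under Randomisations, the two lists differ. R1 is minimised "using the stratification factors; centre, IMWG frailty category, beta-2 microglobulin concentration" and four further laboratory measures. R2 is minimised "using the stratification factors; centre, allocated induction arm (reactive, adaptive); final response to induction treatment". Frailty appears in the first list and not in the second.

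**Role of frailty.** Under Treatment delivery: "The IMWG frailty score was subsequently shown to be predictive of both PFS and toxicity", and "An increase in frailty score was associated with an increased risk of death, progression, non-haematological AEs and treatment discontinuation". The article adds that this association was independent of ISS stage, cytogenetic risk and treatment regimen. It gives no hazard ratio.

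**Availability.** The notes to Figure 4 place the frailty index before R1 and after induction cycles 2, 4, 6 and 12. Trial follow-up adds: "Frailty scores will be completed for all participants at 2, 4, 6 and 12 months post R1".

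**Sizing.** Under Sample size, R2 rests on median PFS of 21 and 29 months, a two-sided 5% level, 80% power, 302 events and 478 participants.

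**The concern.** The trial is built around frailty, and its background section links the score to progression and death, which are the R2 PFS events. A measurement is scheduled at the end of induction. On the natural reading, the R2 primary model nevertheless neither balances on frailty nor adjusts for it.

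Leaving a prognostic covariate out of a Cox model moves the estimated treatment hazard ratio towards 1, compared with the hazard ratio within frailty groups, and gives up some power. The shared phrase also leaves room for doubt. Read broadly, it could bring in the R1 frailty category, measured about a year before R2. A primary model should not depend on which reading is taken.

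**Working it through.** **1. The plan's own figure.** Schoenfeld's formula for 1:1 allocation:

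events = 4(1.960 + 0.842)² / (ln HR)², with HR = 21/29 = 0.724 and ln HR = −0.3228

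= 31.40 / 0.1042 = 301.4, rounded up to **302**. This matches, and power at 302 events is 80.1%. (At the final threshold of 0.047 the same formula gives 79.3%, a difference unrelated to frailty.)

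For participants: with exponential PFS, 30 months of uniform accrual and 24 months of further follow-up, the event probabilities are 0.713 and 0.598, mean 0.655. Then 302 / 0.655 / 0.97 ≈ 475, against 478 stated. Neither step uses a frailty covariate.

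**2. Simulation of the omission.** Document inputs: 478 participants, 1:1 allocation, analysis at 302 events, HR 0.724. Assumptions, because the documents do not give them: a fit/unfit/frail mix at R2 of 55/25/20% (the article expects 45% unfit or frail at R1) and a range of frailty hazard ratios for PFS. There were 3,000 trials per row, tested at two-sided 0.05, with 0.724 taken as the hazard ratio within frailty groups.

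| Unfit / frail HR | HR without → with frailty | Power without → with | Gain (points) |
|---|---|---|---|
| 1.1 / 1.3 | 0.725 → 0.723 | 79.0% → 79.6% | 0.6 |
| 1.2 / 1.7 | 0.726 → 0.721 | 77.6% → 79.8% | 2.2 |
| 1.5 / 2.0 | 0.733 → 0.724 | 76.6% → 78.8% | 2.1 |
| 2.0 / 3.0 | 0.748 → 0.725 | 70.6% → 78.7% | 8.1 |

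Gains are taken before rounding. The simulation error of a single power figure is about √(0.8 × 0.2 / 3000) = 0.7 points.

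The gain does not come from a smaller standard error. In the 1.5/2.0 row the mean standard error of ln HR is 0.1159 without frailty and 0.1163 with it. The signal-to-noise ratio rises from |ln 0.733| / 0.1159 = 2.68 to |ln 0.724| / 0.1163 = 2.78.

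A separate simulation (1,500 trials; HRs 1.4/2.0; mix 50/25/25%; test at 0.047) gave 0.734 → 0.725 and 77% → 80%, a gain of 3 points.

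**3. Response already in the model.** Response is an R2 factor. Assuming 40% below VGPR with HR 1.6, and 4,000 trials per row, the gains for the four rows are about 0, 1.4, 1.9 and 8.1 points.

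**4. Taking 0.724 as the whole-arm hazard ratio.** This is what medians of 21 and 29 months imply. Keeping response in the model and calibrating so that the estimate without frailty is about 0.72:

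| Unfit / frail HR | Power without → with |
|---|---|
| 1.2 / 1.7 | 80.9% → 82.1% |
| 1.5 / 2.0 | 80.3% → 82.9% |
| 2.0 / 3.0 | 80.6% → 87.0% |

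The plan keeps its 80% without frailty, and adding it gives a surplus.

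**5. Validity.** With no treatment effect (frailty HRs 1.2/1.7, 5,000 trials) the rejection rate was 5.4% without frailty and 5.2% with it. The separate simulation, tested at 0.047, gave 4.4% for both. Both models keep the level within simulation error.

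**6. Timing.** Twelve 28-day cycles take 12 × 28 = 336 days, and R2 follows once the end-of-induction response is known. A score taken at 12 months after R1 could therefore fall after R2. The post-cycle-12 score and the month-12 score are not interchangeable.

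**The case against.** The strongest reply is that nothing here is an error. Adjusting for the factors used in the randomisation is standard, the test holds its level, and the test already allows for chance imbalance in an unadjusted covariate. The article also promises a full statistical analysis plan, where extra covariates are often named. All of this stands, and it makes the point a suggested improvement. The point remains worth raising because the article does state the R2 model, in wording that can be read two ways.

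A reader might infer that planned power is lost or that the hazard ratio is biased. The documents do not support this. The 302 events follow from whole-arm medians with no covariate, so 80% power stands for that comparison. The drop to about 77% appears only if 0.724 is taken as the frailty-conditional hazard ratio, which the article never says. Attenuation is likewise relative to that conditional quantity.

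It is also fair that frailty may matter less after R2. The article claims independence from ISS stage, cytogenetics and regimen, but not from depth of response, which is already in the model. Entry to R2 requires 12 cycles, at least a minimal response, no progression, and no intolerance that required stopping either agent. That selection may narrow both the spread and the effect of frailty.

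A reader might also want beta-2 microglobulin added. The article uses it as an R1 stratification factor but says nothing about its effect on PFS after R2, so that extension is not supported.

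**Conclusion.** The point holds as a minor improvement. On the natural reading, the R2 Cox model adjusts for centre, induction arm and response, and leaves out a score that the article itself calls predictive of PFS and schedules at the end of induction. The planned analysis is valid and its stated power is reproduced.

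What is forgone is about 0 to 3 percentage points of extra power for assumed unfit/frail hazard ratios up to about 1.5/2.0, and about 6 to 8 points under an extreme 2.0/3.0. As a scale, moving from 80% to 82% power corresponds to (1.960 + 0.915)² / (1.960 + 0.842)² ≈ 1.05, or roughly 16 more events on 302.

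The frailty hazard ratios, the frailty mix at R2 and the response effect are all assumptions. With a weak frailty effect the gain is close to nil. No OS simulation was run.

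**What to change.** State that the R2 Cox model adjusts for the R2 stratification factors, so that the phrase cannot be read as covering the R1 list.

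Prespecify, before unblinding and preferably before the R2 interim analysis at 151 events (which uses the same model), one further fixed covariate in the R2 PFS and OS models: the last IMWG frailty category recorded before R2. This will normally be the post-cycle-12 score. If it is missing, use the most recent earlier score; the R1 category exists for everyone because it is an R1 minimisation factor. Never use a score taken after R2.

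The cost is a wording change and two model terms against about 302 PFS events, or 180 OS events. No new data are needed. The downside is that the reported hazard ratio becomes conditional on frailty and will differ slightly from the whole-arm ratio implied by the planning medians. A supporting estimate without the frailty term would show the difference.

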#### Secondary endpoint analysis

Secondary endpoint analysis of OS and other time-to-event endpoints will be analysed using similar methods to those described for PFS.

MRD negativity and other binary endpoints will be analysed using similar methods to those described for the early treatment cessation primary endpoint. The number and proportion of participants in each response category (stringent complete response (sCR), complete response (CR), VGPR, etc) will be summarised by allocated treatment and exact 95% CIs will be calculated. The difference in proportions for each response category will be presented with corresponding 95% CIs.

The domains of the QoL questionnaires will be summarised using mean scores adjusted for baseline and 95% CIs at each assessment timepoint. Similar summaries will be produced for quality-adjusted life years (QALYs) derived using the EQ-5D-3L (Euroqol 5 dimensions) questionnaire.

#### Exploratory and subgroup analyses

An overview of the planned exploratory and subgroup analysis can be found in the online supplemental material. These include genetic and molecular analysis of patient samples conducted by the respective central laboratories.

### Health economics

A full HEAP will be written and approved before any analysis is undertaken.

Economic evaluations will be conducted at R1 and R2, using within-trial and decision-model-based analyses. The analysis will be guided by the The National Institute for Health and Care Excellence (NICE) reference case, applying the cost-utility framework from the perspective of the health and social care provider over a life-time horizon. Base case QALYs will be based on EQ-5D-3L responses, and costs on patient completed resource use forms and hospital records. Results will be presented in terms of incremental cost-effectiveness ratios, cost-effectiveness acceptability frontiers and net benefit.

### Trial oversight

The trial management group (TMG) comprises of the chief and co-chief investigators, CTRU team and coinvestigators and are responsible for the clinical set-up, ongoing management, promotion of the trial and for the interpretation of the results. The trial steering committee (TSC), consisting of independent clinicians and statisticians, along with a patient representative, will provide overall supervision on the trial, including trial progress, adherence to protocol, participant safety and consideration of new information.

### Data monitoring

An independent data monitoring and ethics committee (DMEC) will review the safety and ethics of the trial by reviewing unblinded interim data prepared by the CTRU in strict confidence at approximately yearly intervals. Unblinded safety updates are also prepared at 6 monthly intervals. After each annual review of safety data, the DMEC will make their recommendations to the TSC about the continuation of the trial who will make their recommendations known to the TMG.

#### Interim analyses

Two formal interim analyses will be undertaken for early efficacy, one for each of the randomisations. The first will occur when 50% of required participants (370 participants) have reached 60 days post R1. The second will occur when 50% of required PFS events have been observed (151 events) following R2. In order to maintain an overall two-sided 5% significance level for the primary endpoint analysis, the O’Brien and Fleming alpha spending function^30^ will be used. This results in a 0.05% significance level for the interim analysis. The analysis itself will reflect that detailed in the statistical analysis section. For the second interim analysis, only the DMEC, safety statistician and supervising statistician will see the unblinded results, as is standard procedure for double-blind trials.

No other formal analysis of the trial is planned before the participants have attained the primary endpoints.

The DMEC, in the light of the interim data, and any advice or evidence they wish to request, will advise the TSC if there is proof beyond reasonable doubt that one treatment is better and recommend appropriate changes to the trial protocol.

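### The interim level (0.05%) and final level (0.047) are not what O'Brien-Fleming gives at 50% information, and they do not pair with each other

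*Protocol article*

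**What the plan says.** The Interim analyses section of the protocol article states: "Two formal interim analyses will be undertaken for early efficacy, one for each of the randomisations". The R1 look is set by participants: "The first will occur when 50% of required participants (370 participants) have reached 60 days post R1". The R2 look is set by events: "The second will occur when 50% of required PFS events have been observed (151 events) following R2". The stated aim is given as "In order to maintain an overall two-sided 5% significance level for the primary endpoint analysis", the method named is the O'Brien and Fleming alpha spending function, and the outcome is given as "This results in a 0.05% significance level for the interim analysis".

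The final thresholds are in Primary endpoint analysis. For R1: "A statistically significant induction treatment effect will be suggested if the p value for the resulting OR is <0.047". For R2 the same cut-off applies, "if the p value for the HR corresponding to randomisation allocation is <0.047". The Statistical methods section says the 5% level is adjusted on the primary endpoints for the formal interims. No other look or boundary is described.

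**The concern.** Once the overall level, the number of looks, the information fraction and the boundary family are fixed, the interim and final levels follow by calculation. An O'Brien-Fleming boundary halfway through is strict, but 0.0005 is far stricter than it should be. A final level of 0.047 is also lower than any O'Brien-Fleming version leaves after one look at 50%. The two figures point in opposite directions: a very small interim spend should leave the final level almost at 0.05.

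These are the decision rules for both primary endpoints. An interim p value of 0.002, for example, would cross the boundary of the named method but not the printed number. At the final analysis, a p value between 0.047 and about 0.048-0.049 would be non-significant under the printed rule and significant under the named method.

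**Working it through.** **Inputs**
- Overall two-sided level 0.05, O'Brien-Fleming spending, one interim plus one final per randomisation (Interim analyses).
- R2 information fraction t = 151/302 = 0.50 (Interim analyses; Sample size).
- R1 information fraction t = 370/740 = 0.50 as stated. It is 370/720 = 0.514 against the R1 requirement. On unfit and frail participants alone it is 370 × 0.45 = 166.5, and 166.5/324 = 0.514.
- Design effects: 20% v 9% early cessation (R1); median PFS 21 v 29 months, HR 21/29 = 0.724 (R2).

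**The sample-size figures reproduce.** R1: 160 per arm, 320 in total, 320/0.99 = 324 after rounding up, and 324/0.45 = 720. R2: Schoenfeld's formula at HR 21/29 with 80% power gives 302 events. The failure is confined to the significance levels.

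**Formula.** The interim and final statistics have correlation √t = √0.5. For two-sided levels p₁ and p₂ with critical values a and b, overall error = 1 − P(|Z₁|<a, |Z₂|<b).

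**Interim level at t = 0.50**
- Lan-DeMets O'Brien-Fleming type, 0.025 per side: 2 × [2 − 2Φ(2.2414/√0.5)] = 2 × [2 − 2Φ(3.170)] = 0.00305.
- Same function applied to the two-sided 0.05: 2 − 2Φ(1.960/√0.5) = 2 − 2Φ(2.772) = 0.0056.
- Classical O'Brien-Fleming: constant 1.977, interim critical value 1.977/√0.5 = 2.797, p = 0.0052.

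The final level then solves overall error = 0.05.

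| Version | Interim | Final | Overall error |
|---|---|---|---|
| Lan-DeMets O'Brien-Fleming | 0.0031 | 0.0490 | 0.0500 |
| Spending function on two-sided 0.05 | 0.0056 | 0.0478 | 0.0500 |
| Classical O'Brien-Fleming | 0.0052 | 0.0480 | 0.0500 |
| Printed in the protocol | 0.0005 | 0.047 | 0.0471 |

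**Do the printed figures pair with each other?** No. After an interim at 0.0005, the final level that uses up 0.05 is 0.0499. A final level of 0.047 pairs with an interim of 0.0070. The spending function would give 0.0005 only at about 32-37% information.

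**Other readings tried**
- 0.05% as a slip for 0.5%: the final level becomes 0.0481, and 0.005 with 0.047 has overall error 0.0489.
- 0.3% intended, with 0.05 − 0.003 = 0.047: this is simple subtraction rather than the spending function, and overall error is 0.0480.
- R1 at t = 0.514: Lan-DeMets 0.0035/0.0488, two-sided form 0.0063/0.0475, classical 0.0058/0.0478. None gives 0.0005 or 0.047.

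**Effect at the R2 interim (151 events).** Boundary HR = exp(−2z/√151). Expected Z under the design = ln(29/21) × √(151/4) = 0.3228 × 6.144 = 1.98.

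| Interim level | z | HR needed | Chance of crossing |
|---|---|---|---|
| 0.0005 | 3.48 | 0.57 | 6.7% |
| 0.0031 | 2.96 | 0.62 | 16.4% |
| 0.0052 | 2.80 | 0.63 | 20.8% |
| 0.0056 | 2.77 | 0.64 | 21.5% |

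**Effect at the R1 interim.** With 80-83 unfit or frail participants per arm and 20% v 9%, the chance of crossing is 6-7% at 0.0005. It is 16-17% at 0.0031 and 20-21% at 0.0052.

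**Effect overall.** R2 power across both looks (expected final Z = 2.80) is 79.4% with the printed pair, 79.9% with Lan-DeMets and 79.8% with the classical boundary.

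**The case against.** The strongest reply is that the error is conservative. The printed pair spends 0.0471, below the promised 5%, so a significant result under it would still be valid, and the power loss is about half a percentage point. That stands: wrong here means not what the stated method yields, and does not mean that type I error control is lost.

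It can also be said that 0.047 lies within 0.001-0.002 of every version, so the final rule matters only for p values in a narrow band. This too stands. The substantive discrepancy is the interim figure, which may be a decimal slip for 0.5%. That reading is plausible but the document does not confirm it, and it does not rescue the pair, because the matching final level would be 0.0481.

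A third point is that the DMEC weighs other evidence and is not bound by a boundary, and that a full analysis plan will follow. The protocol nevertheless prints exact levels and attributes the interim one to a named calculation. Any later plan would have to depart from either the method or the numbers.

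Reporting 95% confidence intervals beside a threshold of 0.047 is common practice and a minor matter.

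**Conclusion.** The concern holds. At 50% information with an overall two-sided 5%, no standard O'Brien-Fleming version gives 0.0005 at the interim or 0.047 at the final, and the two printed levels do not belong together. The interim level is 6 to 11 times smaller than the named method gives (0.0031/0.0005 = 6; 0.0056/0.0005 = 11). This cuts the chance of crossing at the R2 interim under the design effect from 16-22% to about 7%, with a similar drop for R1. Overall type I error is 4.7%, so there is no inflation, and the loss of overall R2 power is about 0.5 percentage points.

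The result assumes one look per randomisation, the usual correlation √t between looks, and information fractions of 0.50 (R2) and 0.50-0.514 (R1). The conclusion is the same across that range. How the printed figures arose is not stated.

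**What to change.** Name one version and print its pair: Lan-DeMets O'Brien-Fleming with interim p<0.0031 and final p<0.0490, or classical O'Brien-Fleming with 0.0052 and 0.0480. Replace the 0.05% in Interim analyses and both 0.047 rules in Primary endpoint analysis accordingly.

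State that the levels are recalculated from the information fraction actually reached. This matters for R1, where 370 participants may represent 51.4% of the required information; the Lan-DeMets pair would then be 0.0035 and 0.0488. If final confidence intervals are meant to agree with the test, give their level to match.

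The cost is a wording change in the protocol, analysis plan and DMEC charter, made before any unblinded efficacy look. It needs no extra participants or data.
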